## Abstract

**Background:**

The incidence and prevalence of older patients with kidney failure who are dependent on dialysis is increasing. However, observational studies showed limited or no benefit of dialysis on mortality in subgroups of these patients when compared to conservative care. As the focus is shifting towards health-related quality of life (HRQoL), current evidence of effects of conservative care or dialysis on HRQoL in older patients is both limited and biased. Dialysis comes with both high treatment burden for patients and high costs for society; better identification of patients who might not benefit from dialysis could result in significant cost savings. The aim of this prospective study is to compare HRQoL, clinical outcomes, and costs between conservative care and dialysis in older patients.

**Methods:**

The *DIALysis or not: Outcomes in older kidney patients with GerIatriC Assessment* (DIALOGICA) study is a prospective, observational cohort study that started in February 2020. It aims to include 1500 patients from 25 Dutch and Belgian centres. Patients aged ≥70 years with an eGFR of 10–15 mL/min/1.73m^2^ are enrolled in the first stage of the study. When dialysis is initiated or eGFR drops to 10 mL/min/1.73m^2^ or lower, the second stage of the study commences. In both stages nephrogeriatric assessments will be performed annually, consisting of questionnaires and tests to assess most common geriatric domains, i.e. functional, psychological, somatic, and social status. The primary outcome is HRQoL, measured with the Twelve-item Short-Form Health Survey. Secondary outcomes are clinical outcomes (mortality, hospitalisation, functional status, cognitive functioning, frailty), cost-effectiveness, and decisional regret. All outcomes are (repeated) measures during the first year of the second stage. The total follow-up will be a maximum of 4 years with a minimum of 1 year in the second stage.

**Discussion:**

By generating more insight in the effects of conservative care and dialysis on HRQoL, clinical outcomes, and costs, findings of this study will help patients and physicians make a shared decision on the best individual treatment option for kidney failure.

**Trial registration:**

The study was registered in the Netherlands Trial Register (NL-8352) on 5 February 2020.

**Supplementary Information:**

The online version contains supplementary material available at 10.1186/s12882-021-02235-y.

## Background

In the Netherlands, over 6200 patients (358 per million population) with kidney failure are currently dependent on dialysis with an annual incidence of over 1650 patients (95 per million population) [1]. The proportion of older patients has risen over the years and in 2019 45% of the incident dialysis patients were 70 years or older [2]. After dialysis initiation, the overall mortality in this age group is high: 18% in the first year, 72% after 5 years [2]. A Dutch retrospective single-centre study showed no survival benefit from dialysis initiation for patients aged 80 years or older and in those above 70 years with severe comorbidity, compared to conservative care (CC) [3]. These results were confirmed by a prospective multicentre study performed in the Netherlands [4]. Results such as these have shifted the focus from mortality towards health-related quality of life (HRQoL) as the most important outcome [5]. Dialysis is associated with a high treatment burden in older patients when compared to CC [6, 7]. A recent meta-analysis reviewed 11 studies comparing HRQoL between older patients treated with CC or dialysis [7]. All studies had a small sample size, eight were single-centre, and eight were highly susceptible to selection bias and/or confounding. Thus, current evidence for the effects of CC or dialysis on HRQoL is both limited and biased. Despite these limitations, the authors conclude that CC has the potential to achieve similar HRQoL as dialysis.

Outcomes such as survival and HRQoL might differ greatly among older patients with kidney failure due to substantial heterogeneity with respect to functional and cognitive impairment and frailty. Establishing which of these conditions are associated with poor outcome may help to identify those patients at highest risk and thus guide informed treatment decisions [8]. To do this, some authors suggest tailoring the comprehensive geriatric assessments used in geriatric care to routine kidney failure care [9]. However, studies showing the benefit of these assessments on outcomes, such as survival and HRQoL, in these patients are lacking.

Besides the impact on survival and HRQoL, dialysis is also a highly expensive treatment: the costs in the Netherlands approximate € 92,000 per patient per year, making it among the most expensive treatment in internal medicine, both per individual patient as in total treatment costs [10]. If dialysis treatment appears to yield little or no benefit in selected older and/or frail patients, such as improved survival or HRQoL, CC could be considered more often as the preferred treatment option. This may result in significant cost savings for treatment of kidney failure.

Therefore, large and well-designed, prospective, multicentre studies with sufficient follow-up in older patients treated with CC or dialysis are needed. The *DIALysis or not: Outcomes in older kidney patients with GerIatriC Assessment* (DIALOGICA) study aims to compare HRQoL, clinical outcomes, and financial costs between CC and dialysis in patients of 70 years or older with kidney failure. Secondly, the study aims to associate clinical and geriatric patient characteristics in the decision-making trajectory with these outcomes. Our hypothesis is that CC is associated with comparable HRQoL, comparable clinical outcomes, and lower costs, compared to dialysis in subgroups of older patients with kidney failure.

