### Outcome variables

The primary outcome parameter is HRQoL (Table 2). DIALOGICA will assess three secondary outcome parameters: clinical outcomes, cost-effectiveness, and decisional regret. The clinical outcomes that will be assessed are mortality, hospitalisation, functional status, cognitive functioning, and frailty. All outcomes are assessed with (repeated) measures during the first year of the second stage.

**Table 2 Tab2:** Study outcomes

Outcomes			Instruments
Primary outcome	HRQoL		SF-12 physical and mental component scores [28]
Secondary outcomes	Clinical outcomes	Mortality (all-cause)	ERA-EDTA codes [16, 47]
		Hospitalisation (all-cause)	ICD-10 codes [48]
		Functional status	Katz-ADL [14], Lawton-iADL [15]
		Cognitive functioning	MoCA [17], 6-CIT [18], LDST [20]
		Frailty	Clinical Frailty Scale [25]
	Cost-effectiveness		ICERs, calculated using EQ-5D-5 L [30] and iPCQ/iMCQ [32, 33]
	Decisional regret		Decisional Regret Scale [36]

All outcomes are repeated measures during the first year of the second stage (Fig. 1)

*Abbreviations*: *6-CIT* six-item Cognitive Impairment Test, *EQ-5D-5L* Five-level EQ-5D, *ERA-EDTA* European Renal Association - European Dialysis & Transplant Organisation, *HRQoL* Health-Related Quality of Life, *(i) ADL* (Instrumental) Activities of Daily Living, *ICD-10* International Statistical Classification of Diseases, 10th edition, *ICER* Incremental Cost-Effectiveness Ratio, *iMCQ* iMTA Medical Costs Questionnaire, *iPCQ* iMTA Productivity Cost Questionnaire, *LDST* Letter-Digit Substitution Test, *MoCA* Montreal Cognitive Assessment, *QALY* Quality Adjusted Life Year, *SF-12* Twelve-item Short Form Health Survey

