### Sample size calculation

For the primary outcome, we aim to have 80% power to detect a difference of 3.0 points in the SF-12 summary scores 12 months after the start of the second stage. To reject the null hypothesis of equal means with a standard deviation for both groups of 9.0 with a significance level (alpha) of 0.05 using a two-sided two-sample equal-variance Z-test, a required total sample size of 443 patients was calculated (89 patients on CC, 354 on dialysis, 1:4 ratio based on unpublished data from three Dutch centres). When taking into account a dropout rate of 10%, 99 patients on CC and 394 on dialysis are needed, a total of 493 patients. Based on a study from the United States, we expected one third of patients to progress from stage one to two within 3 years, so a cohort of 1500 patients will be needed [49].

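### The hypothesis is comparable HRQoL in subgroups, but the study is sized to detect a difference in the whole cohort, with no margin or rule for concluding comparability

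*Protocol article*

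**What the plan says.** The Background gives a neutral aim, to compare HRQoL, clinical outcomes and costs between CC and dialysis, and then a directional expectation: "Our hypothesis is that CC is associated with comparable HRQoL, comparable clinical outcomes, and lower costs, compared to dialysis in subgroups of older patients".

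The Sample size calculation section describes a different inferential target. It states that "we aim to have 80% power to detect a difference of 3.0 points in the SF-12 summary scores" at 12 months into the second stage. The purpose of the test is "To reject the null hypothesis of equal means", "with a standard deviation for both groups of 9.0" and a "significance level (alpha) of 0.05 using a two-sided two-sample equal-variance Z-test". The result is "a required total sample size of 443 patients was calculated (89 patients on CC, 354 on dialysis, 1:4 ratio"). The calculation covers the whole second-stage cohort and does not mention subgroups.

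Table 2 lists the primary outcome as "SF-12 physical and mental component scores", so there are two primary scores. The Statistical analysis section plans regression and mixed models, with longitudinal results shown as estimates with 95% confidence intervals. The article gives no equivalence or non-inferiority margin and no rule for concluding comparability.

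**The concern.** Comparable HRQoL is a claim that any difference is small enough not to matter. It has to be shown by excluding differences of a stated size. A test of equality works the other way round: rejecting it shows a difference, and failing to reject it shows only that the data did not settle the matter. If the study's own hypothesis is judged by the stated test, the only outcome that could seem to favour it is non-significance, which becomes more likely as numbers fall.

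The subgroup wording sharpens this, because any subgroup is smaller than the cohort that was sized. The stakes are practical. The Background says CC could be preferred more often if dialysis brings little or no benefit, and the Discussion links this to cost savings. An unsupported statement of comparability would feed into those decisions.

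**Working it through.** **Inputs.** All from the Sample size calculation section: difference 3.0, SD 9.0 in both groups, two-sided alpha 0.05, power 80%, allocation 1:4, dropout 10%, one third progressing to the second stage.

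**The plan's own figure.**
- CC: (1 + 1/4) × [9.0 × (1.960 + 0.842) / 3.0]² = 88.3, so 89.
- Dialysis: 4 × 88.3 = 353.2, so 354. Total 443.
- Dropout: 89/0.9 gives 99 and 354/0.9 gives 394. Total 493.
- Cohort: 3 × 493 = 1479, about 1500.

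Every figure reproduces. The arithmetic is right for a difference test.

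**Precision at 89 and 354.**
- SE = 9.0 × √(1/89 + 1/354) = 1.067.
- 95% half-width = 1.96 × 1.067 = 2.09.
- An observed CC deficit just short of significance (2.09) has an interval reaching about 4.18, beyond the plan's own 3.0 points.

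**Chance of a non-significant result when CC is truly worse,** Φ(1.96 − δ/SE):
- δ = 2.0: Φ(1.96 − 1.874) = 0.53.
- δ = 3.0: Φ(1.96 − 2.811) = 0.20.

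**Power to show comparability at a true difference of 0.** The article gives no margin. I assume 3.0, its detectable difference.

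| Claim | Formula | Per score | Both scores, if independent |
|---|---|---|---|
| Non-inferiority, 95% CI above −3.0 | Φ(2.811 − 1.960) | 80.3% | 64% |
| Equivalence, 90% CI within ±3.0 | 2Φ(2.811 − 1.645) − 1 | 75.6% | 57% |
| Equivalence, 95% CI within ±3.0 | 2Φ(2.811 − 1.960) − 1 | 60.5% | 37% |

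For 80% power on one score, equivalence within ±3.0 needs 485 patients (90% interval) or 595 (95% interval) before dropout, against the planned 443. The result depends on the margin: at 2.0, non-inferiority power at 443 falls to 47%; at 4.0 it rises to 96%.

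**Subgroup illustration.** Assume a subgroup of half the cohort, 1:4 allocation within it, and a simple 12-month comparison.
- SE = 1.067 × √2 = 1.509; 95% half-width = 2.96.
- Non-inferiority power at margin 3.0 = Φ(3.0/1.509 − 1.96) = 51% per score.
- Interaction between two such halves: SE = 1.509 × √2 = 2.13; power for a 3-point interaction = Φ(3.0/2.13 − 1.96) = 29%.

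**The case against.** The strongest reply is that the Background's first aim is simply to compare, and a two-sided test is a legitimate basis for sizing that. The comparability sentence is an expectation, confined to subgroups. Longitudinal results will be reported with 95% intervals, which a reader can set against 3.0 points. This stands, and it rules out two stronger readings. A reader might infer that the investigators intend to treat non-significance as proof of comparability; nothing in the article says so. A reader might also infer that the study cannot answer its own question. The figures do not support that for the whole cohort: the half-width of 2.09 is inside 3.0, and the planned size gives about 80% power per score for non-inferiority at that margin.

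A third temptation is to make multiplicity part of the main point, since two tests at 0.05 give a familywise error of up to 1 − 0.95² = 9.75% if independent. That applies only to a claim of difference on either score. Requiring comparability on both scores needs no alpha split. The reading that each score is tested at 0.05 rests on one alpha beside a plural noun, and an analysis plan not shown may settle it.

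It is also fair that the calculations use an unadjusted 12-month comparison, whereas mixed models with confounder adjustment are planned. Actual precision could be better or worse.

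None of this removes the mismatch. Intervals without a margin give no decision rule, and the stated hypothesis and the stated sizing objective remain different claims.

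**Conclusion.** The concern holds as a mismatch between hypothesis and test. The hypothesis is comparability in subgroups; the sizing is for a difference in the whole cohort; nothing fixes how small a difference counts as comparable. The risk is that a non-significant result could be read as support, when it would arise 53% of the time under a true 2-point CC deficit and 20% under a 3-point deficit (89 and 354 patients, SD 9.0).

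For the whole cohort the defect is one of specification and interpretation, and the planned numbers can carry a one-sided claim at a 3.0-point margin. They fall short of 80% for two-sided equivalence, for both scores jointly, and for subgroups. The comparability powers assume a margin the article does not state and a true difference of 0. The joint figures assume independent scores, and the subgroup figures assume a half split.

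**What to change.** Choose one of two routes and record it before results are seen.

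1. Restate the hypothesis as estimating the difference in HRQoL between CC and dialysis, with intervals and no claim of comparability. This costs only wording.
2. Keep the comparability hypothesis and add a rule: CC is called comparable, meaning non-inferior, only if the lower limit of the adjusted 95% confidence interval for CC minus dialysis lies above −3.0 for both the physical and the mental score. Justify 3.0 as a margin, since the article presents it only as a detectable difference. State that a non-significant difference alone does not show comparability.

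Route 2 uses the same data and sample size, but its power should be disclosed: about 80% per score and 64% for both if independent. If two-sided equivalence is meant, say so, and report 76% or 61% per score (90% or 95% interval) or enlarge the study.

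For the subgroup hypothesis, name a few characteristics in advance, report treatment-by-characteristic interactions and subgroup intervals against the same margin, and label them exploratory. State that a half-cohort subgroup would have a half-width of about 3 points. If a difference on either score may be claimed, add a multiplicity rule such as Holm for that claim only.

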## Methods

### Study design

DIALOGICA is a multicentre, prospective, observational cohort study comparing CC with dialysis. The first patient was recruited in February 2020. The study aims to include 1500 patients from at least 25 academic and non-academic centres in the Netherlands and Belgium. DIALOGICA is one of the *Leading the Change* healthcare evaluation projects. *Leading the Change* finances and guides several healthcare evaluation projects in the Netherlands. The programme is financed by Dutch health insurers and aims to increase and implement acquired knowledge from these projects, thereby increasing the effectiveness of the Dutch healthcare system.

The study consists of two stages (Fig. 1). Patients remain in the first stage as long as their estimated glomerular filtration rate (eGFR), as calculated by the Chronic Kidney Disease Epidemiology Collaboration (CKD-EPI) formula or using mean urea and creatinine clearances in 24-h urine collections, stays above 10 mL/min/1.73m^2^. The second stage commences at the start of dialysis or when the eGFR drops to or below 10 mL/min/1.73m^2^. This creates two groups (patients treated with either dialysis or CC) which are used as the main determinant for the study.

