	Dialysis Symptom Index (DSI) [29]	SAQ	30 Questions regarding presence of specific symptoms, when present scored on a 5-point Likert scale. Used in Dutch nephrological care as PRO.	Yes/no, if yes 1 (‘not at all’) to 5 (‘very much’). Total score 0–30 for each ‘yes’, higher scores indicating higher number of symptoms. No cut-off values.
Costs	Five-level EQ-5D (EQ-5D-5L) [30]	SAQ	5 Questions regarding health aspects (mobility, self-care, usual activities, pain/discomfort, anxiety/depression) using a 5-point Likert scale and 1 overall health score on a visual-analogue scale. Used to calculate QALYs in cost-effectiveness analysis	1 (‘no problems’) to 5 (‘unable to/extreme problems’); 0 ‘worst health you can imagine’ to 100 (‘the best health you can imagine’ for the visual-analogue scale. Reference values using Dutch value set [31].
	(subset of questions from) iMTA Productivity & Medical Costs Questionnaire [32, 33]	SAQ	8 General questions and 22 questions on healthcare use in the previous 3 months. Used to calculate healthcare-related costs in cost-effectiveness analysis.	NA
Decisional regret	Treatment Choice Questionnaire & Decisional Conflict Scale (DCS) [34, 35]	SAQ	Questionnaire filled in when treatment choice has been made. Contains 23 questions regarding the choice made.	NA for Treatment Choice Questionnaire; 0–100 for DCS, higher scores indicating higher decisional conflict, no cut-off values.
	Decision Regret Scale (DRS) [36]	SAQ	5 Questions on regret regarding the choice for either conservative care or dialysis on a 5-point Likert scale.	0–25, higher scores indicating stronger feelings of regret. No cut-off or reference values [37].

*Abbreviations*: *CA* Clinician Assessment, *HRQoL* Health-Related Quality of Life, *IAQ* Interviewer-Administered Questionnaire, *iMTA* Institute for Medical Technology Assessment, *PRO* Patient Reported Outcome, *SAQ* Self-Administered Questionnaire, *T* Test, *NA* Not Applicable, *QALY* Quality Adjusted Life Year

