#### Clinical outcomes

Mortality will be analysed as all-cause mortality within the first year of the second stage. The cause of death will also be categorised into seven categories, based on the United Kingdom Renal Registry, using ERA-EDTA codes (Table S2) [16, 47]. Hospitalisation will be analysed as all-cause hospitalisation within the first year of the second stage and each individual episode will be categorised into seven categories, using ICD-10 codes (Table S3) [48]. Functional status, cognitive functioning, and frailty will be repeated measures (at the start of the second stage and after 12 months) using their respective instruments, described in the previous paragraphs.

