### Statistical analysis

All statistical analyses will be performed using statistical software, such as SPSS and R. Univariable and multivariable regression analysis to correct for possible confounders will be used to compare groups. Longitudinal data will be analysed with linear and logistic mixed models and presented as estimated coefficients and odds ratios with 95% confidence intervals. Cumulative incidence of hospitalisation and mortality will be reported in Kaplan Meier curves. A Cox proportional hazards model will be used to compare the rate of mortality and hospitalisation between groups. Overall costs and ICERs will be compared across the two groups using linear regression. Discounting, a mathematical procedure for adjusting future costs to their ‘present day value’, will be applied, as requested for all health economic evaluation exceeding a time frame of 1 year. To deal with missing data, multiple imputation by fully conditional specification will be applied.

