## Discussion

With an ageing population with kidney failure, more patients will face the decisional moment whether to start dialysis or not. As the survival benefit of dialysis treatment in the geriatric population is debatable, focus has shifted towards HRQoL as primary outcome measure. The impact of dialysis on HRQoL of older patients is probably large, but current data comparing it to CC are both limited and biased, creating an urgent need for high-quality studies [7]. DIALOGICA will be the first large study to prospectively assess the differences between patients choosing CC or dialysis. With a total follow-up of up to 4 years, outcome parameters can be assessed in more detail. Biological age, which also takes factors such as functional status, cognitive functioning, and somatic functioning into account, might influence these outcomes more than calendar age. This study will help to determine individual patient characteristics to identify patients less likely to benefit from dialysis initiation. This will support patients with kidney failure and their nephrologists in making a well-informed and shared decision when discussing renal replacement therapy. To do so, DIALOGICA combines a practical test set of well-validated questionnaires and assessments that can be performed in less than 1 hour per patient. With better identification of patients who might not benefit from dialysis, a significant reduction in costs for treatment of kidney failure can be achieved if these patients choose for CC, since CC has far lower annual treatment costs compared to dialysis [6].

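### The stage 2 trigger is said to create the CC and dialysis groups but does not identify treatment, and choice, the basis that would work, is not made the grouping variable

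*Protocol article*

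**What the plan says.** The Study design section keeps patients in stage 1 only while eGFR is above 10. It then gives two alternative entry events: "The second stage commences at the start of dialysis or when the eGFR drops to or below 10" (mL/min/1.73m²). The next sentence derives the exposure from them: "This creates two groups (patients treated with either dialysis or CC) which are used as the main determinant for the study".

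Stage 2 start is also time zero. Under Outcome variables: "All outcomes are assessed with (repeated) measures during the first year of the second stage". Under Clinical outcomes: "Mortality will be analysed as all-cause mortality within the first year of the second stage". Under Statistical analysis: "A Cox proportional hazards model will be used to compare the rate of mortality and hospitalisation between groups". That section states no rule for a patient who starts dialysis after entering stage 2 through eGFR.

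The Discussion describes the contrast differently: "DIALOGICA will be the first large study to prospectively assess the differences between patients choosing CC or dialysis". Table 1 shows that the choice is collected, through the Treatment Choice Questionnaire: "Questionnaire filled in when treatment choice has been made". No visible text says that this record defines the groups.

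**The concern.** Reaching eGFR 10 says nothing about which treatment a patient is on or intends. A patient who plans dialysis but has not started when eGFR reaches 10 cannot stay in stage 1, so enters stage 2 undialysed. The text leaves two direct ways to label that patient as treated with one or the other:

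- **By the trigger.** The patient counts as CC, and the CC group takes in people heading for dialysis.
- **By dialysis received later in the first year.** The patient moves to the dialysis group and brings the waiting time along. Nobody in that group can die during the wait, so that time is immortal. Those who die while waiting stay in CC and count as CC deaths.

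The first dilutes differences in SF-12, function, cognition, frailty and regret. The second distorts mortality, and outcomes that depend on survival. The remedy offered in the Discussion is correction for patient characteristics, which addresses confounding by indication but repairs neither of these. Dilution also pushes towards the hypothesis in the Background, that HRQoL is comparable.

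**Working it through.** **1. The plan's own sample size.** Inputs from the Sample size calculation section: difference 3.0, SD 9.0, two-sided alpha 0.05, power 80%, ratio 1:4.

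n(dialysis) = (1.96 + 0.8416)² × 9² × (1 + 4) / 3² = 353.2, so 354. n(CC) = 354/4 = 88.5, so 89. The total is 443, as stated. Dividing by 0.9 gives 394 and 99, total 493, also as stated. There is no arithmetic error.

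**2. SF-12 under trigger-based grouping.** Let a share f of the 354 dialysis patients enter through eGFR and be labelled CC. Assume that their mean score is that of the dialysis group. Then:

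- labelled CC = 89 + 354f; labelled dialysis = 354(1 − f)
- observed difference d = 3.0 × 89 / (89 + 354f)
- power = Φ(d / [9√(1/n_CC + 1/n_D)] − 1.96)

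| f | Labelled CC / dialysis | Dialysis-bound share of CC | Difference | Power |
|---|---|---|---|---|
| 0 | 89 / 354 | 0% | 3.00 | 80% |
| 10% | 124.4 / 318.6 | 28% | 2.15 | 62% |
| 20% | 159.8 / 283.2 | 44% | 1.67 | 47% |

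The 1:4 ratio is why a small leak matters: 10% of the larger group is over a quarter of the relabelled CC group. The documents do not give f.

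**3. Mortality under grouping by treatment received in the first year.** All inputs here are assumptions, with no true effect of treatment:

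- Death hazard h = 0.20 per year in everyone (1 − e^(−0.20) = 18%). The 18% in the Background is measured after dialysis start; applying it to CC and waiting patients is an assumption.
- 80% choose dialysis, in line with the 1:4 ratio.
- A share s of dialysis-choosers enters stage 2 at dialysis start. The rest enter at eGFR 10 and wait an exponential time with mean m.

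With k = h + 1/m, per waiting patient over one year:

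- deaths before dialysis: a = (h/k)(1 − e^(−k))
- person-years of those never dialysed: b = h[1 − (1 + k)e^(−k)]/k² + e^(−k)

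Per patient in general, deaths are D = 1 − e^(−h) = 0.1813 and person-years P = D/h = 0.9063.

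Example with s = 0 and m = 0.5 year: k = 2.2, a = 0.0808, b = 0.1375.

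- Labelled CC: deaths 0.2 × 0.1813 + 0.8 × 0.0808 = 0.1009; person-years 0.2 × 0.9063 + 0.8 × 0.1375 = 0.2912; rate 0.347
- Labelled dialysis: deaths 0.8 × (0.1813 − 0.0808) = 0.0803; person-years 0.8 × (0.9063 − 0.1375) = 0.6151; rate 0.131
- Ratio CC:dialysis = 2.65, where the truth is 1.0

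Across the range (in brackets, the share of patients labelled CC who had chosen dialysis):

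| Choosers entering at dialysis start (s) | Mean wait 3 months | 6 months | 12 months |
|---|---|---|---|
| 0% | 2.40 (20%) | 2.65 (43%) | 2.43 (63%) |
| 50% | 1.63 (11%) | 1.73 (28%) | 1.54 (46%) |
| 75% | 1.30 (6%) | 1.36 (16%) | 1.28 (29%) |
| 90% | 1.12 (2%) | 1.15 (7%) | 1.12 (14%) |

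A simulation of 2,000,000 patients per cell agrees with these ratios to within 0.01. In the same simulated data, grouping by choice at time zero gives about 1.0, and so does dialysis as a time-dependent exposure.

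**The case against.** The strongest reply is that a sound reading is available. The Discussion repeatedly describes patients who choose CC or dialysis, the choice is recorded when made, and grouping by it removes the spurious ratio in the check above. A reader might infer that no reading of the plan gives a valid comparison; the documents do not support that. What stands is that the one sentence defining the main determinant refers to treatment, derives it from a trigger that does not identify treatment, and is not reconciled with the Discussion.

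Second, Fig. 1 and the full protocol are not shown and may hold the rule. Time-dependent exposure could properly be left to an analysis plan, and the Cox model as named does not exclude it. This limits how firmly bias can be predicted. It does not rescue the visible sentence, which states a rule rather than leaving one open.

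Third, a reader might take 2.40–2.65 as the size of the bias, or conclude that every comparison is shown to be biased. Neither follows. Those ratios need every dialysis-chooser to enter through eGFR, and they concern mortality only. Immortal time does not directly shift an SF-12 score; the issue there is dilution, and only under trigger-based grouping.

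**Conclusion.** The concern holds as a badly fixed exposure definition. Taken literally, the Study design rule either labels dialysis-bound patients as CC or, if they are relabelled by later treatment, gives them immortal time. Grouping by choice would largely avoid both but is nowhere stated as the rule in the visible text.

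The direction is clear: treatment-received grouping makes CC mortality look too high, and trigger-based grouping makes SF-12 look too similar. The size is not known. It depends chiefly on the share of dialysis-choosers who enter stage 2 at dialysis start, then on the wait from eGFR 10 to dialysis; the documents give neither. The mortality ratios also assume equal hazards in all patients, and the SF-12 figures assume that relabelled patients score like the dialysis group. Because the definition underlies the primary comparison, it should be settled before analysis even if the true leak is small.

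**What to change.** Reconcile the Study design section with the Discussion:

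- Define the primary exposure as the treatment choice documented at or before stage 2 start, and keep it fixed.
- State one time zero for everyone: first eGFR of 10 or lower, or dialysis start if that comes earlier.
- Add a supportive analysis with actual dialysis start as a time-dependent exposure.
- Report the share of dialysis-choosers who start dialysis, and the share who die before starting.
- Analyse patients undecided at time zero in a sensitivity analysis.

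The cost is wording plus a dated choice field; the questionnaire already collects the choice, and no extra patients are needed. There are two downsides. The primary contrast becomes chosen strategy rather than dialysis received. The mixed trigger also still leaves some difference in eGFR between groups at time zero, which needs adjustment. None of this implies any rule for when dialysis should start.
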